**Aim 4. Effectiveness of EHR-based frailty screening**								
Association of EHR frailty indices with functional status	VA-FI, JEN FI	X		X	X	X		X

Abbreviations: *CDW* Corporate Data Warehouse, *GECDAC* GEC Data & Analysis Center, *RHF* Residential History File, *VA-FI* VA Frailty Index

### Phase 2: Implementation (12 months)

The Implementation periods, shown in Fig. 3, are as follows.

### Run-in period (standard implementation; 3 months)

We will implement the packaged intervention and local adaptations using the standard implementation strategy bundle (coalition building, implementation champions, local technical assistance, system-level audit and feedback). We chose this as the standard approach because its use resulted in 100% Reach in prior work and because use of champions (i.e., individuals who dedicate themselves to supporting and implementing an intervention) are associated with increased uptake of primary care interventions [55–57].

#### Standard implementation strategy bundle

Build a Coalition: We will cultivate relationships with primary care and nursing leadership at each site, with the goal of increasing leadership awareness and buy-in for implementation efforts. To do so, the Implementation Team will facilitate meetings with site leaders to update them on implementation and elicit their feedback on project challenges to guide implementation efforts.Implementation Champions: One nurse and one PCP at each site will serve as Implementation Champions. Champions will help to facilitate problem-solving for the workflow of their site as it relates to implementing the intervention. Champions will receive monthly audit and feedback reports and will be responsible for sharing findings with other clinicians at their site.Local Technical Assistance: The Implementation Team will partner with clinicians, champions, and leadership to problem-solve issues related to implementation as they arise. Depending on site needs, additional technical assistance may include one-on-one meetings and weekly office hours to establish feedback channels to report on local progress and enhance buy-in and trust [48].System-level Audit and Feedback: Reports on Reach and proportion of patients with functional impairment at each site will be sent monthly by the Implementation Team to Clinical Champions and site leadership (e.g., medical center directors, nurse executives, PACT medical directors, nurse managers).

#### Period 1 (Randomization to Standard or Enhanced Implementation; 3 months)

Our adaptive trial design will deploy resources to sites with the greatest need for enhanced implementation strategies [32–34]. After the Run-In period, data generated by the clinical screening tools (“Health Factors” data) will be used to identify sites with inadequate Reach, defined as < 80% of eligible veterans receiving LVN screening and/or PCP assessment (in keeping with standard benchmarks for adequate adherence to practice guidelines) [58]. We will define PCP assessment as reviewing LVN screening results and either (1) documenting via checkbox that further referral is not needed or (2) placing a referral to address identified impairments. We chose both LVN screening and PCP assessment as the benchmark for implementation response because these combined steps contribute to improved identification (via screening) and management (via assessment/referrals). Sites with ≥ 80% Reach at the end of the Run-In phase will receive the standard implementation bundle for all phases of implementation. For sites with < 80% Reach, we will randomize 1:1 by site to 3 additional months of standard vs. enhanced implementation. Based on current levels of functional status measurement in VA primary care practices (51% measuring function among ≥ 80% of eligible veterans), we anticipate that half of included sites (*n* = 4) will require enhanced implementation. The enhanced implementation strategy bundle will include the components of the standard bundle above (i.e., Coalition Building, Implementation Champions, Technical Assistance) plus clinician-level audit and feedback for participating LVNs and PCPs instead of site-level audit and feedback.

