**Methods:**

We will conduct a hybrid type 2 implementation-effectiveness cluster-randomized adaptive trial at 8 VHA sites using the Practical, Robust Implementation and Sustainability Model (PRISM) to guide implementation and evaluation. During a Pre-Implementation phase, we will engage clinical partners and develop local adaptations to maximize intervention-setting fit. During an Implementation phase, we will launch a standard bundle of implementation strategies (coalition building, champions, technical assistance) and system-level audit and feedback, identify sites with low uptake, and randomize those sites to receive continued standard vs. enhanced strategies (standard strategies plus clinician-level audit and feedback). The primary implementation outcome is reach (proportion of eligible patients at each site who receive screening/assessment) and the primary effectiveness outcome is appropriate management of impairment (proportion of patients with identified impairments who receive related referrals).

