**Supplementary Information:**

The online version contains supplementary material available at 10.1186/s43058-025-00698-w.

Contribution to the literature
Maintaining functional status, or the ability to perform daily activities such as bathing, dressing, and preparing meals, is central to older adults’ quality of life, health, and ability to remain independent, and identifying functional impairments is essential for clinicians to provide optimal care to older adults.The Patient-Aligned Care Team (PACT) Functional Status Screening Initiative is an evidence-based, patient-centered, low burden intervention to increase identification and improve management of functional impairment among older adults.Studies have not evaluated the adoption of routine, standardized functional status screening within a large national health care system.This study will evaluate the implementation of the PACT Functional Status Screening Initiative across 8 VA sites to assess (1) Reach (percentage of eligible patients who are screened and assessed for functional impairment) and (2) proportion of patients with identified impairment who receive appropriate care.

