**3. Electronic tools and templates to facilitate LVN screening, PCP assessment, and documentation**
• **Component 3a:** Validated LVN screening tool: (1) brief two-question pre-screener asking about difficulty performing ADLs and IADLs [41], and, among patients who report difficulty on pre-screener, (2) in-depth screener asking about difficulty and needing help with each ADL/IADL [42]. Results used to auto-populate nursing note • **Rationale:** Two-part screener intended to quickly identify patients who would benefit from in-depth screening while “screening out” individuals without impairment, reducing LVN and patient burden. Automation reduces documentation burden
• **Component 3b:** PCP alert and referral menu: If patient screens positive (i.e., reports difficulty/needing help with ≥ 1 ADL/IADL), PCP receives electronic alert linked to referral menu. Alert prompts PCP to review LVN screening results and perform additional assessment as needed. PCP can select up to 5 referrals: physical therapy, occupational therapy, social work, geriatric medicine, prosthetics; referral menus may be adapted at each site to meet local needs and include Community Care referrals • **Rationale:** Addresses clinical partner requests for integration of functional assessment into existing workflows and need for a standardized location to retrieve data on function; alert supports interprofessional approach to measurement; integrated EHR referrals address concerns that data will not be used to inform care and that clinicians lack knowledge of resources, making desired outcome (appropriate referral) more salient for PCPs

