### Outcome measures and sources by aim

#### Aim 1 (Implementation Outcomes)

The primary outcome for Aim 1 is Reach, with secondary outcomes of Adoption, Implementation (fidelity, adaptations), and Maintenance (Table 3). Reach is defined as the proportion of eligible Veterans who receive LVN screening and PCP assessment at each site. We will identify eligible veterans (i.e., ≥ 60 years old, seen in primary care after implementation begins) and use Health Factors to identify completed screening, defined as an LVN completing the electronic tool, and assessment, defined as a PCP reviewing screening results and either (a) documenting via checkbox that further referral is not needed or (b) placing a referral to address impairments.

Adoption is defined as the proportion of LVNs and PCPs at each site who regularly complete screening and assessment. Adequate adoption is defined as ≥ 80% [58]. To identify more nuanced aspects of adoption, we will review a randomly selected subset of charts at each site to examine if clinician notes for the visit when screening was completed have content related to functional status and type of content.

Fidelity to intervention core components will be assessed to determine if core components were implemented as intended, accounting for adaptations and modifications that were consistent vs. inconsistent with intent [48]. Study staff will complete fidelity checklists using electronic health record and qualitative data sources.

Recipient experience will be assessed using periodic reflections for champions, interviews for leadership, veterans, and family caregivers, and surveys for clinicians, and will be used to inform adaptations to intervention components and implementation strategies [59]. To operationalize processes within PRISM’s Adoption, Implementation, and Maintenance domains, we will use Normalization Process Theory (NPT) to guide qualitative data collection [39, 40]. NPT complements PRISM and considers the intervention itself, how staff understand the intervention, attitudes that develop around the intervention, and how it fits into existing roles, systems, and norms. We will use qualitative data to investigate how these processes and constructs shaped implementation and sustainment outcomes.

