#### Aim 2 (Implementation Strategy Effectiveness)

The primary outcome for Aim 2 is Reach, defined as in Aim 1, with ≥ 80% defined as adequate Reach (Table 2). We will assess perspectives on the effectiveness of the standard vs. enhanced implementation strategies using qualitative data.

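### Reach, which serves as primary outcome, randomisation trigger and crossover rule, is worded in two ways, and neither literal wording fits a PCP step that is prompted only after a positive screen

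*Protocol article*

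**What the plan says.** All references are to the protocol article.

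- **Trigger.** The Period 1 section calls Reach inadequate when fewer than 80% "of eligible veterans receiving LVN screening and/or PCP assessment". A little further on it says "We chose both LVN screening and PCP assessment as the benchmark for implementation response".
- **Primary outcome.** Under Aim 1 (Implementation Outcomes): "Reach is defined as the proportion of eligible Veterans who receive LVN screening and PCP assessment at each site". Eligible veterans are those aged 60 or over seen in primary care once implementation has begun; the definition has no restriction to positive screens. Aim 2 takes it over: "The primary outcome for Aim 2 is Reach, defined as in Aim 1, with ≥ 80% defined as adequate Reach".
- **Other wordings.** The abstract has "proportion of eligible patients at each site who receive screening/assessment", where the slash can be read either way. The contribution box has "percentage of eligible patients who are screened and assessed for functional impairment".
- **Workflow.** In Table 1, Component 2 makes the PCP's follow-up depend on the screening score. Under Component 3b, it is when the patient screens positive that the "PCP receives electronic alert linked to referral menu".
- **PCP assessment.** In both Period 1 and Aim 1 this means reviewing the LVN's results and then either ticking that no further referral is needed or placing a referral.
- **Use.** Reach against 80% decides which sites are randomised (Period 1) and which standard-arm sites cross over (Period 2). The proportion of sites at or above 80% is the Aim 2 primary outcome in the analysis plan.

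**The concern.** One variable selects the sites for randomisation, governs the crossover and forms the Aim 2 endpoint. It is stated with two different connectives, and the Period 1 section uses *and/or* and then *both* within one paragraph. This is not detail left to a later document: the article states the definition, and states it inconsistently.

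The workflow adds a second difficulty. A veteran who screens negative has been handled as intended, but the article describes no prompt by which that veteran would acquire a PCP assessment, and no passage says that a negative screen counts as complete. With 8 sites and about 4 expected to be randomised, moving even one site across the 80% line changes the randomised comparison. An unsettled trigger also leaves room to choose its meaning after the run-in data are seen.

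**Working it through.** **The plan's own figure.** Period 1 expects half the sites (n = 4) to need enhanced implementation, from 51% of practices measuring function in at least 80% of eligible veterans. 8 × (1 − 0.51) = 3.92, so 4 is reproduced. The input is a rate of measuring function; PCP assessment is not mentioned. The planning figure therefore supports only a screening-type reading of Reach.

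**Notation.** Let s be the proportion of eligible veterans screened by an LVN, p the share of screens that are positive, and a the proportion of positive screens with a PCP assessment. Assume that assessments are recorded only after the positive-screen alert.

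- Either step suffices: Reach = s. Assessment is a review of LVN results, so assessed veterans are a subset of those screened, and a drops out.
- Both steps required, read literally: Reach = s × p × a.
- Conditional (screened and, if positive, assessed): Reach = s × (1 − p) + s × p × a.

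**Value for p.** The only prevalence in the article is in the Background: 459,000 / 2,800,000 = 0.164, for ages 65 and over. Eligibility starts at 60, and a positive screen means difficulty or needing help with at least one activity, so 16.4% is a stand-in. Higher values are shown as assumptions.

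| s | p | a | Either step | Literal both | Conditional |
|---|---|---|---|---|---|
| 100% | 16.4% | 100% | 100% | 16.4% | 100% |
| 100% | 30% | 100% | 100% | 30% | 100% |
| 100% | 60% | 100% | 100% | 60% | 100% |
| 100% | 16.4% | 0% | 100% | 0% | 83.6% |
| 85% | 16.4% | 50% | 85.0% | 7.0% | 78.0% |
| 90% | 30% | 50% | 90.0% | 13.5% | 76.5% |

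**Reading the table.**

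1. With perfect delivery (s = a = 1), the literal *both* reading gives Reach = p. It reaches 80% only if at least 80% of eligible veterans screen positive. For any smaller share, 8 of 8 sites fall below the trigger, every standard-arm site stays below it at the crossover check, and the Aim 2 endpoint is zero in both arms.
2. Under *either step*, a fully screened site with no PCP assessment scores 100%, against the stated choice of both steps as the benchmark.
3. The conditional reading can also part from *either step* at the threshold. At s = 85%, p = 16.4%, a = 50%: 0.85 × 0.836 + 0.85 × 0.164 × 0.5 = 0.780, so the site is randomised; under *either step* it scores 85.0% and is not.
4. At p = 16.4%, the conditional composite is still 1 − 0.164 = 83.6% with full screening and no PCP assessment, so it cannot by itself show whether the PCP step is happening.

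**The case against.** **The two wordings may be meant to agree.** The Period 1 phrase defines *inadequate* Reach, so *and/or* may mean that a site fails if it falls short on screening, on assessment, or on both. The enhanced bundle's monthly lists use the same construction for patients who missed a step, and the sentence about choosing both steps would then be a clarification. This reading is possible and would align Period 1 with Aim 1. It leaves the second difficulty untouched: with both steps required of all eligible veterans, correctly handled negative screens still have no described way into the numerator.

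**The ceiling is an assumption.** Nothing forbids a PCP from reviewing a negative screen and ticking that no referral is needed, and score-dependent follow-up could be taken to imply assessment only where indicated. Both points stand. The ceiling is therefore conditional, and the 16% depends on the stand-in for p. The conditional intention is plausible, but no passage states it.

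**Stronger readings that the article does not support.**

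- A reader might infer that the denominator accumulates from the start of implementation, making 80% hard to recover after a poor run-in. The text says when eligibility begins, not that counts are pooled across periods; Reach is reassessed at Period 2, and the models are longitudinal.
- A reader might infer that the planning rests on a third, screening-only meaning, because the run-in section says of the standard bundle that "its use resulted in 100% Reach in prior work" while the Background reports that pilot result as screening. The pilot is used to justify the choice of bundle; the expected 4 sites come from the 51% figure. Whether the pilot also measured assessment cannot be seen here.
- A reader might infer that Aim 1 succeeds or fails on this definition. Its analysis plan looks at whether baseline characteristics are associated with Reach and sets no 80% success test.

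**Conclusion.** The definition is wrong as written and needs to be settled. The difference in wording is plain on the page and does not depend on any assumption. If either step suffices, Reach equals the LVN screening rate and the PCP step plays no part. If both are required of every eligible veteran, Reach is capped at the positive-screen share, provided PCPs do not record assessments for negative screens. The cap is about 16% with the age 65+ prevalence as stand-in, and it stays below the trigger for any share under 80%. In that case all 8 sites, not 4, would be low uptake however well they deliver.

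It would go too far to say that no site can reach 80%, or that the two wordings must classify sites in opposite ways. The first depends on how negative screens are recorded, and the second on reading *and/or* as *either*.

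**What to change.** Adopt one definition of Reach and use it in Period 1, Period 2, the Aim 1 and Aim 2 outcome sections and the Aim 2 analysis plan, with the abstract brought into line: a veteran is reached if the LVN screen is complete and, when it is positive, the PCP assessment is complete as well, over all eligible veterans. This takes the Table 1 workflow as it stands. If the team intends PCPs to record a review of negative screens too, the workflow and the definition must be reconciled.

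Beside the composite, report LVN screening among eligible veterans and PCP assessment among positive screens. These are descriptive components, not a second threshold, and they guard against a composite near 84% that hides an absent PCP step.

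The cost is protocol wording and a changed query on Health Factors data already being collected. The downside is that some sites which would pass on screening alone may fall below 80%, as in the 85.0% versus 78.0% example, so the expected number of randomised sites should be reconsidered. If any site has already been classified, state which reading was used.

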## Methods

### Overview of study design

We will implement and evaluate the PACT Functional Status Screening Initiative using a hybrid type II implementation-effectiveness [43] cluster-randomized adaptive design (Fig. 2) [32–34]. We chose a hybrid type II design because the intervention is supported by promising preliminary data, but the evidence is not yet fully established, and current rates of screening suggest that more intensive implementation strategies may be needed to improve adoption [28]. Because individual implementation sites may have different needs, we will use an adaptive design to determine if more intensive efforts are needed to improve adoption in sites with low uptake. To include an appropriate comparison group, sites with low uptake will be cluster randomized to a standard vs. enhanced bundle of implementation strategies. The design includes a crossover phase so that all of the low uptake sites receive enhanced implementation.

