**Fig. 2 Fig2:**
[figure not shown]
Flow Diagram for Adaptive Cluster-Randomized Controlled Trial. The figure shows the sequence of the four implementation periods, randomization, and cross-over allocation

In keeping with our operational partners’ interest in developing proactive approaches to identify high-risk veterans and intervene to prevent or delay functional impairment and associated acute care utilization, we will test the association of clinic-collected functional status measures with automated EHR-based frailty measures. Because frailty typically develops before functional impairment and may be a promising target for intervention [44–47], these findings will clarify how the two approaches might complement and inform one another.

Based on Primary Care and Office of Nursing Services capacity and input, we will implement the intervention in two waves, with 8 sites total. Sites may range in size depending on organizational capacity (e.g., a full community-based clinic or several primary care teams within a larger site). For both waves, we will cluster at the site level. Each site will move through three phases: Pre-Implementation, Implementation, and Sustainment (Fig. 3) [48].

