#### Period 2 (Crossover Allocation; 3 Months)

At the beginning of Period 2, we will assess Reach and perform crossover allocation. Sites that were initially randomized to standard implementation and are still non-responsive (< 80% Reach) will cross over to enhanced implementation. Sites that were randomized to standard implementation and achieve ≥ 80% Reach will continue to receive standard implementation. Sites randomized to enhanced implementation will receive standard implementation regardless of response.

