#### Analysis plan, aim 2 (Implementation Strategy Effectiveness)

The primary outcome for Aim 2 is the proportion of sites that achieve ≥ 80% Reach. As in Aim 1, we will first describe site characteristics by implementation strategy bundle (standard vs. enhanced) and baseline proportions of screening and assessment. We will also fit mixed effects logistic regression models where the unit of analysis is the site, accounting for the longitudinal (repeated measures) design and for covariates such as level of champion engagement. Our primary interest is effectiveness of the standard vs. enhanced approach. Inference will be determined using odds ratios and 95% CIs and/or p-values. A similar strategy will be employed for secondary outcomes. We will compare recipient perspectives on the standard vs. enhanced approach using methods as in Aim 1 and triangulate qualitative and quantitative data on effectiveness of strategy bundles [65].

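### The primary standard-versus-enhanced comparison in Aims 2 and 3 is not tied to the sites, period and arm that are randomised, and the Aim 3 power statement counts sites expected never to be randomised

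*Protocol article*

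**What the plan says.** - **Purpose of randomising** (Overview of study design): "To include an appropriate comparison group, sites with low uptake will be cluster randomized to a standard vs. enhanced bundle of implementation strategies".
- **Number of sites** (same section): "we will implement the intervention in two waves, with 8 sites total".
- **Period 1.** For sites under 80% Reach, "we will randomize 1:1 by site to 3 additional months of standard vs. enhanced implementation". About half of the sites (n = 4) are expected to be in this group. For sites at or above 80%, the text reads "Reach at the end of the Run-In phase will receive the standard implementation bundle for all phases of implementation".
- **Period 2.** The enhanced bundle goes to this group: "Sites that were initially randomized to standard implementation and are still non-responsive". Standard-arm sites that reach 80% stay on standard. For the other arm: "Sites randomized to enhanced implementation will receive standard implementation regardless of response".
- **Period 3.** Every site is on standard.
- **Analysis plan, aim 2.** The outcome is the proportion of sites at or above 80% Reach, analysed by site-level mixed logistic models with repeated measures. "Our primary interest is effectiveness of the standard vs. enhanced approach".
- **Analysis plan, aim 3.** The same contrast is the primary inference for effectiveness, from logistic mixed models.
- **Table 3.** Aim 3 outcomes are marked at pre-implementation, Periods 1, 2 and 3, and 6 months. The run-in column is not marked.
- **Missing data and power analysis.** 730 participants are said to give 80% power for Aim 3, set against an available sample of more than 5,000 veterans from 8 sites.
- **Overview of study design, on the crossover:** "The design includes a crossover phase so that all of the low uptake sites receive enhanced implementation".

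**The concern.** Bundle received equals bundle assigned at random only in Period 1, and only among low-uptake sites. Outside that cell, three other things determine exposure:

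1. High-uptake sites are on standard because they already met the 80% threshold. For Aim 2 that threshold is also the outcome.
2. In Period 2, a site is on enhanced because it failed on standard.
3. In Periods 2 and 3, standard includes sites that have just had enhanced, so any lasting benefit is credited to standard.

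The analysis sections do not keep these apart from the randomised contrast, and the power statement suggests that all 8 sites are meant to contribute. The comparison group that randomisation was introduced to provide could then be lost in the primary estimate of two aims.

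**Working it through.** **1. Where exposure is randomised**

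| Sites | Period 1 | Period 2 | Period 3 |
|---|---|---|---|
| At or above 80% at run-in (about 4) | standard, by selection | standard | standard |
| Below 80%, assigned enhanced (about 2) | enhanced, randomised | standard, after enhanced | standard, after enhanced |
| Below 80%, assigned standard (about 2) | standard, randomised | enhanced if still below 80%, otherwise standard | standard, some after enhanced |

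**2. The plan's sample size**

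Inputs from the power section: effect size 0.40, α = 0.05, power 80%, design effect 4.4. Two-sided, n per arm = 2(1.960 + 0.842)²/0.40² = 98.1, or 99 with the t correction. Then 99 × 2 × 4.4 = 871, not 730. The stated 730 is 730/8.8 = 83 per arm, about 73% power. This is a separate matter and does not affect the present point.

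**3. What restriction to randomised sites does to the Aim 3 sample**

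Assumptions: equal site sizes and a total of 5,000.

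- Veterans: 5,000 × 4/8 = 2,500.
- The Aim 3 denominator is veterans with impairment. The protocol does not say whether the 5,000 are eligible or impaired veterans. Its Background gives 459,000/2.8 million = 16.4% for ages 65 and over.
- If the 5,000 are eligible veterans: 5,000 × 0.164 = 820 impaired at 8 sites, 410 at 4 sites.
- Power = Φ(0.40 × √(N/8.8/2) − 1.96). This is 0.78 for N = 820 and 0.49 for N = 410.
- If all 2,500 are impaired, nominal power exceeds 0.99, but still from four clusters.

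**4. Information in 2 versus 2 sites**

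There are C(4,2) = 6 possible allocations, so the smallest two-sided permutation p is 2/6 = 0.33. With 49% of sites low-uptake (the complement of the protocol's 51%), the chance of at most one randomisable site is 0.51⁸ + 8 × 0.49 × 0.51⁷ = 0.04.

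**5. Bias of an as-exposed analysis**

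The design was simulated (4,000 replicates) on parameters that are not in the documents: 8 sites, mean Reach 80% on the logit scale, between-site SD 1, period SD 0.5, trend 0.2 logit per period. Models with more than one period have a random site intercept and period effects. Entries are odds ratios (exponentiated mean logit estimates).

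| Analysis | No true effect | True OR 1.65, no carry-over | True OR 1.65, 80% carry-over |
|---|---|---|---|
| Randomised sites, Period 1 | 0.98 | 1.62 | 1.63 |
| All sites, Period 1 | 0.40 | 0.66 | 0.65 |
| All sites, Periods 1-3 | 0.92 | 1.51 | 1.18 |
| Randomised sites, Periods 1-3, as exposed | 0.99 | 1.60 | 1.29 |
| All sites, run-in to Period 3 | 0.99 | 1.62 | 1.34 |

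The first row differs from 1.00 and 1.65 only by simulation error. At 40% carry-over the all-site Period 1-3 value is 1.33.

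Varying the inputs with no true effect (between-site SD 0.5 to 1, trend 0 to 0.6) gives 0.40-0.70 for all sites in Period 1, 0.89-0.92 for Periods 1-3 and 0.98-1.00 with run-in included. Without period effects, the Period 1-3 value ranges from 0.47 to 0.93.

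The direction can also reverse. With site fixed effects, run-in included and no true effect, regression to the mean gives about 1.26 (run-in plus Period 1) and 1.08 (run-in to Period 3).

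**The case against.** The protocol nowhere says that high-uptake sites enter the comparison. The study objectives and the design overview both describe comparing bundles among low-uptake sites, and the exact analysis set is often left to a statistical analysis plan, which is not shown here. The Aim 2 model uses repeated measures, so the large distortion from an all-site Period 1 cross-section belongs to an analysis that the protocol does not propose. In the kind of model it does describe, selection bias is small, and the heavier attenuation needs an assumed carry-over. Restricting to Period 1 also gives up the crossover information and leaves about four sites.

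Much of this stands. A reader might infer that the planned estimate is biased against enhanced, or that it would favour standard when enhanced works. The documents do not support that: they leave the model open, and the result runs from strong bias against enhanced, through almost none, to slight bias in its favour. The simulations also use continuous logit Reach, whereas Aim 2 analyses a yes/no site outcome and Aim 3 analyses referrals.

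What does not stand is that this is only omitted detail. The power section, read with the Aim 3 analysis plan, counts all 8 sites for a contrast that the design overview sets up among low-uptake sites only. The run-in baseline that removes most of the selection bias is not marked for Aim 3 in Table 3, and neither analysis plan specifies it for this contrast.

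**Conclusion.** The concern holds in this form: the primary contrast of Aims 2 and 3 is not tied to the only randomised comparison in the design, and the Aim 3 power statement conflicts with that comparison. The textual evidence is stronger for Aim 3. For Aim 2 the site set is simply unstated.

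No single size of bias can be given. Under the assumed parameters it ranges from severe (OR about 0.4 under no effect, all-site cross-section), through modest (about 0.9, Periods 1-3 with random intercept), to negligible (about 1.0 with run-in included). A true OR of 1.65 becomes about 1.5 without carry-over and about 1.2 with 80% carry-over in the all-site Period 1-3 model.

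Separately, the design overview says that all low-uptake sites receive the enhanced bundle, while the Period 2 text keeps responding standard-arm sites on standard. This is a smaller inconsistency that needs no calculation.

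**What to change.** - **Primary contrast.** State for Aims 2 and 3 that standard versus enhanced is estimated in the randomised low-uptake sites, by assigned arm, on Period 1 outcomes, adjusting for run-in Reach where available.
- **Other data.** Report high-uptake sites and Periods 2-3 as secondary or descriptive, with prior enhanced exposure as a separate model term.
- **Power.** Restate the sample and power for the randomised sites only, and say whether the counts are eligible or impaired veterans.
- **Interpretation.** Acknowledge that about 2 versus 2 sites makes the contrast largely an estimation exercise.
- **Crossover.** Reconcile the design overview with the Period 2 text.

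Trial conduct need not change for the analysis points. The cost is more than wording, however. The primary contrast rests on about half the sites, its interval will be wide, and a mixed logistic model on four yes/no site outcomes cannot be relied on for valid intervals. The power claim may fall well below 80% (0.49 under the assumptions above).
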